**Figure 2 figure2:**
[figure not shown]
Graphic presentation of the delineation: clinical target volume (CTV)-para-aortic lymph node (LN)+CTV pelvic LN: purple; CTV prostate bed: red; bladder: yellow; sigmoid colon, small intestine, and large bowel: green; femoral heads: brown; bone marrow: light blue; kidneys: turquoise; spinal cord and cauda equina: marine blue.

**Figure 3 figure3:**
[figure not shown]
Dose distribution in para-aortic radiotherapy trial. Top: coronal dose distribution (dose range: 0-70 Gy); bottom: transverse dose distribution clinical target volume-para-aortic lymph node (dose range, 0-50 Gy).

### Dose Prescription and Treatment Delivery

Dose will be prescribed as D_98_ (ie, the dose received by 98% of the volume and a surrogate for minimal dose) to the PTV of the pelvic LN and PALN. This D_98_ is 45 Gy, to be delivered in 25 fractions of 1.8 Gy. In case of the postprostatectomy situation, the PTV of the prostate and seminal vesicle bed will be treated with a median dose of 70 Gy in 35 fractions. In case of primary radiotherapy to the prostate, the median PTV dose will be 65 Gy in 25 fractions (moderate hypofractionation). Details on dose prescription and constraints for OARs are provided elsewhere [16]. Treatment will be delivered using 6 to 10-MV photons from a linear accelerator (both Elekta and Varian Systems are used). Image-guided radiotherapy is obligatory and will be performed using daily cone-beam CT [35].

### Hormonal Treatment

ADT will be started 2-4 weeks before the start of radiotherapy to overcome the androgen receptor-induced radioresistance [36]. The duration of ADT is 24 months (long term) as all patients belong to a very high-risk population and long-term ADT is the standard of care in these patients [37,38]. Of note, both the use of an luteinizing hormone-releasing hormone-analogue and an antagonist is allowed.

### Primary Endpoint

The primary endpoint is 5-year clinical relapse-free survival (cRFS), defined as the absence of any cR that would be visible at top of the line imaging (see below). Any detected clinical recurrences (r) would be anatomically mapped and categorized as local (rL), pelvic nodal (rN1), retroperitoneal nodal (rM1a), bone (axial, perpendicular, or both, rM1b), or soft-tissue (rM1c). Combinations of different relapse sites are of course possible and will be reported accordingly. Apart from the anatomical site of relapse, the number of relapses, size per relapse, and the subsequent treatment will be recorded.

PSA measurements are performed during follow-up according to a fixed schedule (Table 1). If PSA is undetectable, patients are considered free of cR. In case of biochemical relapse, defined as PSA >0.2 µg/L in the postprostatectomy setting and PSA >nadir+2 µg/L in the primary setting [39,40]. In addition, positron emission tomography-CT (PET-CT) imaging using prostate-specific membrane antigen ligand or ^18^F/^11^C-choline- based PET-CT imaging is acquired. Additional imaging tools include multiparametric MRI and MRI of the axial and perpendicular bones. The decision to perform additional imaging will be taken after multidisciplinary consensus in all cases.

**Table 1 table1:** Standard Protocol Items: Recommendations for Interventional Trials 2013 diagram: Para-Aortic Radiotherapy (PART)-trial.

Timepoint		Study period					
		Enrollment: Screen visit & pre-PART (-t_1_)	Postallocation				
			During PART		Follow-up		
			Weekly	Last day	Month 1, 3, 6, 9, 12	Month 18, 24, 30, 36, 42, 48, 54, 60	Year 6 up to year 10, yearly

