**Assessments**							
	Clinical examination	X		X	X	X	X
	Laboratory analysis^b^	X		X	X	X	X
	Registration of pretreatment gastrointestinal and genitourinary morbidities^b^	X					
	Registration quality of life using validated questionnaires	X		X	X	X	X
	Registration of PART-induced toxicity (Common Toxicity Criteria for adverse events)^b^		X	X	X	X	X
	Imaging (after discussion at an interdisciplinary tumor board)	X			X^c^	X^c^	X^c^

^a^Elective PART occurs during the whole period—daily instead of weekly, including the last day.

^b^Standard examinations; laboratory analysis is described in the protocol.

^c^In case of prostate-specific antigen relapse or symptoms.

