Time to palliative ADT is defined as the secondary endpoint of this trial. Indications to initiate palliative ADT are based on the EAU guidelines [39,40] and include the following: PSA>50 µg/L or PSA doubling time <6 months or symptoms due to progressive disease. In case of oligometastatic recurrence (1-3 synchronous metastases), metastasis-directed therapy is the preferential treatment option [48]. Time to CRPC is defined according to the criteria defined in the EAU guidelines [39,40]. CSS is defined as the interval from the date of diagnosis to the date of death from PCa or to the last follow-up date for censoring purposes, if the patient is alive and is still being followed at the time of data cut-off.

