### Sample Size and Statistics

We aim to improve 5-year cRFS by 15% (primary endpoint). This would result in a 5-year cRFS of 75% compared with the control group with WPRT only that reaches a 5-year cRFS of 60% [18,20]. For a log-rank test comparing two survival curves with a one-sided significance level of .1, assuming uniform accrual with an accrual time of 48 months and a follow-up time of 12 months, a sample size of 137 is required to obtain a power of at least 80%. Taking into account a dropout of 10%, we aim to include 151 patients. The control group consists of pN1 patients treated with adjuvant ADT and WPRT alone from whom the data have been published before [20]. The incidence of acute and late toxicity will be recorded. In addition, actuarial risk estimates for developing acute and late toxicity will be calculated using Kaplan-Meier analysis. Time to palliative ADT, time to CRPC, CSS, and in-field pelvic and para-aortic disease control will be calculated using Kaplan-Meier actuarial analysis. cRFS, time to CRPC, CSS, and in-field pelvic and para-aortic disease control times are defined from the date of LN dissection until an event or last follow-up. Statistical analysis will be performed using the latest version of SPSS (IBM Corp, Armonk, NY, USA).

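### Palliative ADT can start on PSA criteria before any lesion is visible, and the printed cRFS definition does not allow for this: in scan-negative men a primary event can be delayed past 5 years or missed

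*Protocol article*

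**What the plan says.** Five statements in the protocol article bear on this point.

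- **Event (Primary Endpoint).** cRFS is "defined as the absence of any cR that would be visible at top of the line imaging". No other event is named.
- **PSA rule (Primary Endpoint).** "If PSA is undetectable, patients are considered free of cR". The rule does not separate PSA that is undetectable because the disease is controlled from PSA that is undetectable because ADT was restarted.
- **Imaging (Primary Endpoint; Table 1, footnote c).** At biochemical relapse (PSA above 0.2 µg/L after prostatectomy, nadir + 2 µg/L in the primary setting) PET-CT "based PET-CT imaging is acquired". The printed sentence is broken, but this is its natural reading. Beyond that, "The decision to perform additional imaging will be taken after multidisciplinary consensus in all cases". Imaging in follow-up takes place "In case of prostate-specific antigen relapse or symptoms". No scheduled scan is described, and no repeat scan after a negative one.
- **Palliative ADT (Secondary Endpoints).** The indications are alternatives: "PSA>50 µg/L or PSA doubling time <6 months or symptoms due to progressive disease". Two of the three are PSA criteria, and none requires a visible lesion. Time to palliative ADT is a separate secondary endpoint.
- **Time at risk (Sample Size and Statistics).** cRFS and the other listed "disease control times are defined from the date of LN dissection until an event or last follow-up". Starting ADT is neither an event nor a censoring point.

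**The concern.** Treatment given for PSA failure can affect whether the primary event is ever observed. Take a man beyond his 24 months of adjuvant ADT whose PSA crosses the relapse threshold, whose PET-CT is negative and whose doubling time is under 6 months. He meets an indication for palliative ADT. If his PSA then falls, the PSA trigger for imaging is silent. If it becomes undetectable, the endpoint rule itself classes him as free of clinical relapse. Unless symptoms or a new PSA rise lead to imaging in time, he passes year 5 without an event, although his disease has failed and been treated.

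The trial's own hypothesis treats palliative ADT as an outcome to be postponed, yet an early start can help the primary result. The comparison is also open and non-concurrent: PART patients are recruited from 2017 at several centres, and the controls were treated at one centre between January 2000 and January 2016. If the use of ADT for PSA-only failure differs between the two, the cRFS curves can separate, or fail to separate, for reasons unrelated to para-aortic irradiation.

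**Working it through.** **1. Which patients are exposed**

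- PSA >50 µg/L: the PET-CT thresholds (0.2 µg/L, or nadir + 2 µg/L) are far lower, so a scan is due long before this criterion is met. This route is nearly empty.
- Symptoms: these trigger imaging under Table 1, so this route is largely covered.
- Doubling time <6 months with a negative PET-CT: no later imaging is prescribed unless PSA relapses or symptoms appear. This is the route that remains.
- Calendar: all patients receive 24 months of ADT, begun 2-4 weeks before radiotherapy, and cRFS runs from lymph node dissection. A new start of palliative ADT can therefore mask relapses only in roughly years 2 to 5.

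**2. The plan's own figure**

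Inputs (Sample Size and Statistics): 5-year cRFS 60% vs 75%, one-sided α = .10, power 80%, 48 months' accrual, 12 months' follow-up. With exponential survival, HR = ln 0.75 / ln 0.60 = 0.563. Required events are 55 (Schoenfeld) or 58 (Freedman). Event probabilities are 0.259 (control) and 0.157 (PART), mean 0.208. This gives 132 to 140 per group, so the stated 137 is reproduced as a per-group number. Power is 0.81 with 137 per group, and 0.83 with 137 against the 154 published controls (Results).

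**3. Illustration: no true effect, masking in the PART group only**

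The masked share m of relapses is an assumption, since the document gives no figure. True 5-year cRFS is 60% in both groups, n = 137 and 154, with complete 5-year follow-up.

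- Apparent PART cRFS: S = 1 − 0.40(1 − m)
- HR = ln S / ln 0.60
- Events: D = 137(1 − S) + 154 × 0.40
- Chance of a positive test: Φ(√[D·p(1 − p)] × |ln HR| − 1.2816), with p = 137/291 = 0.471

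| m | S | HR | D | Chance of a positive test |
|---|---|---|---|---|
| 0 | 60% | 1.000 | 116.4 | 0.10 |
| 5% | 62% | 0.936 | 113.7 | 0.18 |
| 10% | 64% | 0.874 | 110.9 | 0.28 |
| 20% | 68% | 0.755 | 105.4 | 0.56 |

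A comparison of two proportions agrees. At 10% masking, 0.04/0.0569 = 0.70, giving 0.28. At 20%, 0.08/0.0561 = 1.43, giving 0.56.

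**4. Illustration: planned effect true, equal masking in both groups**

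The formulas are the same, with control cRFS 1 − 0.40(1 − m) and PART cRFS 1 − 0.25(1 − m).

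| m | Control | PART | Difference | HR | D | Power |
|---|---|---|---|---|---|---|
| 0 | 60% | 75% | 15.0 points | 0.563 | 95.9 | 0.94 |
| 10% | 64% | 77.5% | 13.5 points | 0.571 | 86.3 | 0.91 |
| 20% | 68% | 80% | 12.0 points | 0.579 | 76.7 | 0.87 |

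The starting power of 0.94 exceeds the planned 0.80 because complete 5-year follow-up is assumed here, against 12 months after accrual in the plan's calculation. The article places the primary analysis at a median follow-up of 60 months, so both tables are approximations.

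**The case against.** The strongest case for the plan has four parts.

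*The safeguard is real.* PET-CT is due at low PSA thresholds, so many lesions will be seen before ADT is considered. A reader might infer that any man given ADT for PSA failure then stays relapse-free through year 5. The document does not support that. Symptoms still trigger imaging, PSA and testosterone are measured at every visit, a PSA rise on ADT can prompt a scan, and a lesion found later still counts. A falling PSA is also not an undetectable one. Events may often be delayed rather than lost. This stands and narrows the point.

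*The size is assumed.* A reader might take a false-positive rate of 0.28 or 0.56 as a property of the trial. It is not. It requires masking in the PART group and none in the controls, and nothing in the article describes ADT timing or imaging in the control series. More masking among the controls would bias against PART. This stands in full.

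*Ignoring later therapy is a recognised approach.* Following patients to relapse whatever treatment they receive is legitimate, and detail on new therapy is often left to an analysis plan, which is not shown. This stands in part. The approach needs the event to remain observable, and the article itself prints both the event definition and an undetectable-PSA rule that has no exception for salvage ADT.

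*A composite primary endpoint has its own fault.* A reader might conclude that ADT start should become a primary event. That would put unblinded treatment decisions directly into the primary endpoint and break the link with the 60% and 75% planning figures. This stands, and it is why the fix leaves the primary endpoint imaging-based.

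**Conclusion.** The concern holds in limited form. As printed, the endpoint lets salvage ADT started on PSA criteria delay or prevent observation of the primary event, and it classes a man as free of clinical relapse if that ADT makes his PSA undetectable. The men affected are mainly those with a negative PET-CT and a short doubling time, after adjuvant ADT has ended.

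Neither the size nor the direction of any bias against the historical controls can be derived from the document. Under the assumption of 5-20% masking in the PART group only, the nominal .10 error rate would become about 0.18-0.56. Under equal masking of 10-20%, the loss is small: power of about 0.91-0.87 instead of 0.94. The result is therefore sensitive to a difference in salvage practice between the groups, and much less so to masking shared by both. The printed analysis does not show which of these applies.

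**What to change.** Keep imaging-visible relapse as the primary endpoint and make two additions.

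1. State in the endpoint definition that, for patients on salvage ADT, undetectable PSA does not by itself establish freedom from clinical relapse.
2. Prespecify a sensitivity analysis of the primary log-rank test, reported beside it. It counts the start of palliative ADT, or of other salvage treatment for PSA failure before visible relapse, as an event on its start date. Apply the same rule to the PART and control data.

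**Cost.** This needs one definition sentence and one further analysis. For PART patients, the start of palliative ADT is already needed for a secondary endpoint; start dates of other salvage treatment before a visible relapse may have to be added. For the 154 controls, salvage start dates must be extracted, and the article does not show whether they are available. Sensitivity cRFS will be lower than primary cRFS and is not directly comparable with the 60% and 75% planning figures. The analysis also reflects clinicians' timing of ADT, so it should be read as a check on the primary conclusion, not a replacement for it. No change to care is proposed.

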## Results

Ethical approval to conduct this study (version 2.0 from December 1, 2016) was granted by the Medical Ethics Committee University Hospitals/Catholic University Leuven (14/12/2016). Written informed consent of patients is mandatory before recruitment. Recruitment of patients started in 2017 and is expected to be completed by March 2020.

As a result of the PART trial, we will publish the 5-year cRFS, defined as the absence of any cR that would be visible at top of the line imaging, our primary endpoint. Furthermore, we will compare these results with the 5-year cRFS of a historical control group of patients who underwent WPRT; the results of this historical control group have already been published by Poelaert et al [20]. This control group includes patients with PCa who underwent PLND and pelvic radiotherapy between January 2000 and January 2016 at a tertiary center (GUH). Those patients were rigorously treated by several authors of this manuscript ([name], VF, [name], and NL). A total of 154 pN1 patients with PCa who received WPRT were included. As described in the “Sample size and Statistics” section, survival curves of both groups will be compared using log-rank test. Besides, acute toxicity and QoL results will be published after short-term follow-up, whereas treatment-related late toxicity and QoL results, time to palliative ADT, time to CRPC, CSS, and in-field pelvic and para-aortic disease control will be published after a longer follow-up period.

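### The unqualified rule that undetectable PSA means no clinical relapse conflicts with the imaging-based primary endpoint; read literally, it drops relapses found on symptom-triggered imaging

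*Protocol article*

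**What the plan says.** The Primary Endpoint section makes three statements that bear on what counts as an event.

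- The endpoint is 5-year cRFS, "defined as the absence of any cR that would be visible at top of the line imaging". This is a definition by imaging.
- "Any detected clinical recurrences (r) would be anatomically mapped and categorized as local (rL), pelvic nodal (rN1", and so on through the other sites. No PSA condition is attached.
- After mentioning scheduled PSA measurements, it adds: "If PSA is undetectable, patients are considered free of cR". PET-CT follows in case of biochemical relapse, "defined as PSA >0.2 µg/L in the postprostatectomy setting and PSA >nadir+2 µg/L in the primary setting".

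Table 1, footnote c, gives the trigger for follow-up imaging: "In case of prostate-specific antigen relapse or symptoms". Symptoms alone are therefore enough.

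Hormonal Treatment states: "The duration of ADT is 24 months (long term"; this applies to all patients in the trial.

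On the comparator, Sample Size and Statistics says: "The control group consists of pN1 patients treated with adjuvant ADT and WPRT alone from whom the data have been published before". The Results section adds: "A total of 154 pN1 patients with PCa who received WPRT were included". Neither place says how relapse was ascertained in that series, or whether a PSA rule was used.

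**The concern.** The protocol provides for imaging in patients who have no PSA relapse, yet its only classification rule for undetectable PSA says that such patients have not relapsed. If a patient develops symptoms, is imaged, and has a confirmed metastasis while PSA is undetectable, the endpoint definition makes this an event and the PSA sentence makes it a non-event. Two people coding the same record could disagree on the primary endpoint.

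The situation can arise during the 24 months of ADT, which make up 24/60 = 40% of the 5-year window. That ADT can hold PSA down is general clinical knowledge and is not stated in the protocol.

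The comparison is with a published series and not with a randomized group. Nothing in the design ensures that both groups share one event definition, so a rule that removes events from one group may not remove the same events from the other.

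**Working it through.** **Step 1: the statements side by side.** Take a patient with undetectable PSA, symptoms, and a relapse confirmed on imaging.

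| Source | Status of this patient |
|---|---|
| Endpoint definition (imaging) | Event |
| Mapping of detected recurrences | Recorded as a recurrence |
| PSA sentence, read literally | No event |
| Table 1, footnote c | Imaging is foreseen, so the case can occur |

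No sentence gives one statement precedence over another.

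**Step 2: the plan's own sample size.** Inputs from Sample Size and Statistics: 5-year cRFS of 75% against 60%, one-sided 0.10, accrual a = 48 months, follow-up f = 12 months, n = 137, power of at least 80%.

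- HR = ln(0.75)/ln(0.60) = 0.563.
- With exponential survival, λ = −ln(S)/60 and event probability p = 1 − [exp(−λf) − exp(−λ(a+f))]/(λa). This gives 0.2588 (control) and 0.1567 (PART).
- With 137 per group, expected events are d = 137 × (0.2588 + 0.1567) = 56.9.
- Schoenfeld: power = Φ(√(d/4) × |ln HR| − 1.2816) = 81.2%. Freedman: power = Φ(√d × (1 − HR)/(1 + HR) − 1.2816) = 79.6%.

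Read as 137 per group, the stated figure is consistent with its inputs. The PSA rule does not enter it.

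**Step 3: what the rule could do.** Let s be the share of relapses by year 5 that the literal rule removes. The protocol gives no value, so 0% to 20% is an assumed range. A relapse masked early whose PSA later rises is imaged and counted then. It is delayed and not lost, so s covers only relapses that stay masked to year 5.

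*Scenario A: relapses removed in PART only, counted in controls, no true effect.*

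- Observed PART cRFS = 1 − 0.40(1 − s).
- Apparent HR = ln(observed cRFS)/ln(0.60).
- With 137 against 154 patients, all followed for 60 months, d = 137 × 0.40(1 − s) + 154 × 0.40 and π = 137/291.
- P(reject) = Φ(√(dπ(1 − π)) × (−ln HR) − 1.2816).

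*Scenario B: same rule and same s in both groups, true difference of 15 points.*

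- Observed difference = (0.40 − 0.25)(1 − s).
- With no true effect, both groups shift equally and there is no bias.

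| s (assumed) | A: PART cRFS | A: apparent HR | A: P(reject), nominal 10% | B: observed difference |
|---|---|---|---|---|
| 0% | 60.0% | 1.000 | 10.0% | 15.0 points |
| 2% | 60.8% | 0.974 | 12.7% | 14.7 points |
| 5% | 62.0% | 0.936 | 17.7% | 14.3 points |
| 10% | 64.0% | 0.874 | 28.4% | 13.5 points |
| 20% | 68.0% | 0.755 | 56.3% | 12.0 points |

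The two scenarios point in opposite directions, and the protocol does not say which one applies.

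**The case against.** The strongest reply is that the PSA sentence belongs to a work-up sequence: measure PSA on schedule, presume no relapse if it is undetectable, image if there is biochemical relapse. On that reading it gives only the default status of patients who are not imaged. The imaging-based definition and the unconditional mapping of detected recurrences support this. The reading is plausible and may be what was meant, so it is too much to say that the rule overrides imaging-proven relapse. But the sentence as published has no such limit, and the benign reading has to be supplied by the reader.

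A reader might go further and infer that the endpoint is biased in favour of PART. The protocol does not support that. It would require that relapses at undetectable PSA were counted in the historical controls, and relapse ascertainment there is not described. The controls also received ADT, so PSA suppression does not by itself separate the groups. Under a common rule the effect works against PART.

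It can also be said that adjudication detail belongs in the full protocol or analysis plan. That would answer a complaint about missing detail. Here the article states a rule that conflicts with its own endpoint definition, and a later document would have to contradict the published sentence to repair it.

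**Conclusion.** The point stands as an internal conflict in the definition of the primary endpoint. Read literally, the PSA sentence scores an imaging-confirmed relapse at undetectable PSA as event-free, against the endpoint definition in the same section and the symptom trigger in Table 1.

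Neither size nor direction can be fixed from the protocol. The figures under Scenario A rest on three assumptions: the rule is applied literally, the controls were classified differently, and a share s of relapses stays masked to year 5. If s is small, the effect is small even then: about 13% false positives at s = 2%, against a nominal 10%. Under Scenario B there is no false-positive inflation, only attenuation by the factor (1 − s). The stated sample size is not affected.

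**What to change.** Replace the PSA sentence with a rule such as: a patient with undetectable PSA and no symptoms is counted as event-free at that visit without imaging; any relapse confirmed on imaging or histology counts as a clinical relapse on the date of confirmation, whatever the PSA.

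Then confirm that the event definition behind the control group's cRFS is the same. If it differs and cannot be aligned from the existing records, report the difference as a limitation of the comparison.

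The cost is a short wording change and a check of the existing data on the 154 controls, treated between January 2000 and January 2016. That check is the larger part of the work. No new imaging is needed, because symptom-triggered imaging is already in Table 1.

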### Inclusion and Exclusion Criteria

Men aged >18 years with histologically proven adenocarcinoma of the prostate at biopsy (cT1-4) who are referred for primary high-dose radiotherapy or patients after radical prostatectomy (RP; pT2-4) with presence of pN1 disease after ePLND are eligible for the study. pN1 disease is defined as the presence of regional LN metastasis in the true pelvis. These regions include the common iliac nodes, presacral nodes, external and internal iliac nodes, and obturator nodes [27]. In all participating centers, performing an ePLND is the standard of care in high- intermediate and high-risk patients, independent of whether the primary treatment is RP or high-dose radiotherapy [7,28]. If pN1 disease is present, patients are eligible if one of the following criteria is fulfilled:

Two or more positive LNsPositive LNs/removed LNs >7%Presence of extracapsular metastatic extension at the level of any LN

ePLND is defined as the removal of LNs around the external and internal iliac vessels and in the obturator fossa. Removal of additional LNs in the presacral area or around the common iliac vessels is at the discretion of the treating physician (but strongly advised if present on preoperative imaging). The minimum harvest of removed LNs that is considered representative is set at 14. Textbox 1 summarizes the inclusion and exclusion criteria.

After amending, patients with pN1 disease in the salvage setting will be allowed in the PART trial and will be prospectively followed with the same treatment protocol and study design to obtain data about acute and late toxicity. These data will be analyzed separately and will not interfere with the initial set-up of statistics.

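### Relapse imaging is triggered at different PSA levels after prostatectomy and after primary radiotherapy, but the primary log-rank test is stated without stratifying by setting, so a difference in treatment mix from the historical controls would bias it

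*Protocol article*

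**What the plan says.** Five statements in the protocol article bear on this point.

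- **Endpoint.** Under Primary Endpoint, 5-year cRFS is "defined as the absence of any cR that would be visible at top of the line imaging". An event therefore needs a scan.
- **When scans are done.** The footnote to imaging in Table 1 restricts follow-up imaging: "In case of prostate-specific antigen relapse or symptoms". No routine follow-up imaging is scheduled.
- **PSA threshold.** The definition under Primary Endpoint opens with "In case of biochemical relapse, defined as PSA >0.2" and gives in full "PSA >0.2 µg/L in the postprostatectomy setting and PSA >nadir+2 µg/L in the primary setting"; the text then goes on to PET-CT. The sentence holding the definition is incomplete, but read with the table footnote the link from PSA relapse to imaging is clear.
- **Who is enrolled.** Inclusion and Exclusion Criteria admits men "who are referred for primary high-dose radiotherapy or patients after radical prostatectomy (RP; pT2-4) with presence of pN1 disease after ePLND". No share is fixed for either setting.
- **Primary test.** Sample Size and Statistics bases the calculation on one test: "For a log-rank test comparing two survival curves with a one-sided significance level of .1". Results repeats that "survival curves of both groups will be compared using log-rank test". The comparator is 154 pN1 patients treated at one centre between January 2000 and January 2016. Neither section mentions strata or adjustment, and the split of the controls by primary treatment is not given.

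**The concern.** The time at which a clinical relapse is recorded depends partly on when imaging is triggered. After prostatectomy the PSA trigger is 0.2 µg/L; in the primary setting it is at least 2 µg/L, about ten times higher. A lesion that would already be visible can therefore be recorded later in a primary-radiotherapy patient, simply because the scan comes later.

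Within one setting this does no harm to the comparison. It matters when settings are pooled and their shares differ between the groups. Nothing in the design balances those shares: PART is not randomised and recruits from 2017 at two university hospitals and other centres, while the controls come from one centre in an earlier period. A cohort with more primary-radiotherapy patients would then show a better cRFS curve with no effect of para-aortic irradiation. At stake is the error rate of a one-sided .10 test that the article presents as a possible basis for a randomised phase III trial.

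**Working it through.** **1. The plan's own figure.** Inputs from Sample Size and Statistics: 5-year cRFS 60% vs 75%, one-sided alpha .10, power at least 80%, 48 months of uniform accrual and 12 months of follow-up. With exponential survival:

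- HR = ln(0.75)/ln(0.60) = 0.563.
- Event probabilities: 0.259 (control) and 0.157 (PART).
- Size per group: 132.4 (Schoenfeld, 55 events), 138.2 (Lachin-Foulkes), 139.6 (Freedman, 58 events).
- Power with 137 per group: 81.2%.

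The stated 137 is reproduced closely as a per-group size. The present point does not change it; it concerns the validity of the test.

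**2. How large could the delay be?** The article gives no delay, so this is an assumption with a range. Take a nadir of 0.1 µg/L (assumed), so the primary-setting trigger is 2.1 µg/L:

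- log2(2.1/0.2) = 3.39 PSA doublings.
- Doubling time 6 months (assumed): 3.39 × 6 = 20.4 months.
- Doubling time 3 months (assumed): 3.39 × 3 = 10.2 months.

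These are gaps between PSA thresholds. The endpoint delay is shorter if a lesion is not yet visible at 0.2 µg/L or if symptoms prompt imaging. I therefore use 5, 10 and 20 months, with 20 as the upper end.

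**3. Apparent 5-year cRFS with no treatment effect.** Hazard = −ln(0.60)/60 = 0.00851 per month. With delay L, the apparent 5-year cRFS of primary-radiotherapy patients is exp(−0.00851 × (60 − L)). A 20-point difference in mix shifts the pooled value by 0.20 × (that figure − 0.600).

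| Delay | Primary-radiotherapy 5-year cRFS | Shift in pooled 5-year cRFS |
|---|---|---|
| 5 months | .626 | 0.5 points |
| 10 months | .653 | 1.1 points |
| 20 months | .711 | 2.2 points |

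**4. Type I error of the unstratified log-rank.** Simulation with 136 or 137 PART patients vs 154 controls, no PART effect, exponential relapse with 60% at 5 years, a fixed delay in primary-radiotherapy patients, the same triggers in both cohorts, and censoring uniform over 36 to 84 months (assumed). Nominal one-sided level .10.

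| Delay | PART 50%, controls 30% primary radiotherapy | PART 30%, controls 50% |
|---|---|---|
| 5 months | .12 | .08 |
| 10 months | .14 | .06 |
| 20 months | .21 | .04 |

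Two further checks:

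- With equal mix (30% in both), the error is .096 to .106 for delays of 6 to 24 months.
- Stratified by setting, it is .09 to .11 throughout.

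Monte Carlo error is about half a percentage point.

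**5. Power under the planned effect.** With equal mix and a 20-month delay, power in this simulation is about .90 with or without stratification. With PART at 30% and controls at 50%, it falls to about .81 unstratified and stays near .90 stratified.

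**The case against.** The strongest reply has five parts.

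- **The bias is conditional.** The article gives the mix for neither cohort. The 30% and 50% shares are assumptions, and with equal shares there is no bias. This stands: neither the existence nor the direction of the bias can be asserted.
- **The missing strata are inferred from silence.** A short statistics paragraph in an article may leave strata to the full protocol or an analysis plan. This stands in part. However, the article names the primary test twice, both times as a plain comparison of two curves, while making event detection depend on setting. Stratification is a concrete improvement on the test as stated.
- **Two thresholds are legitimate.** They are setting-specific definitions for which the article cites sources. This stands in full; the weak point is the pooled comparison, not the definitions.
- **A reader might infer that relapse is recorded 20 months later after primary radiotherapy.** The article does not support that. The event is visible relapse, not a PSA value. A prostatectomy patient scanned at 0.2 µg/L with a negative scan has no event, symptoms are a second trigger, and additional imaging depends on multidisciplinary consensus. Hence the range from 5 months.
- **Stratification may not suffice.** The imaging triggers used for the 2000–2016 controls are not given. If they differed from those in PART, detection would differ within each setting too. This stands and limits what the fix can achieve.

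The shift in 5-year cRFS is also small beside the 15 points sought. That is true, but a shift of 1 to 2 points still moves a one-sided .10 test noticeably at this sample size.

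**Conclusion.** The point holds as a conditional risk. The primary endpoint is detected under triggers that differ by setting, and the stated test does not account for setting in a non-randomised comparison where nothing balances the mix. With an assumed delay of 5 to 20 months and a 20-point difference in mix, one-sided type I error is about .12 to .21 if PART has more primary-radiotherapy patients and about .08 to .04 if it has fewer, against .10. The false difference in 5-year cRFS is 0.5 to 2.2 points.

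These figures rest on exponential relapse, a fixed delay, the same triggers in both cohorts and the assumed censoring. One might infer that the PART result will be biased in favour of the new treatment; the article does not support that, because it gives neither mix nor delay, and the bias could go either way or be absent. The change is worth making because it is cheap and the risk is foreseeable.

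**What to change.** In Sample Size and Statistics, prespecify that the primary log-rank test, and any Cox model for cRFS, is stratified by primary local treatment (radical prostatectomy vs primary radiotherapy). Report the share of each setting in both cohorts. Give 5-year cRFS by setting, or standardised to the PART mix.

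Cost: the variable is known for every PART patient, since it determines the radiotherapy prescription and the PSA definition. For the controls it is needed at patient level, in the same records that a patient-level log-rank test already requires. Two strata cost no material power.

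Limit: stratification removes only the bias due to mix. The plan should say how relapse imaging was triggered in the controls. If it differed from PART or cannot be established, that should be stated as a remaining limitation of the comparison.
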